#### Compensation Details

Participants will receive US $200 for completing all rTMS treatments (sham and active). They will receive up to US $75 for completing all 3 follow-up visits (US $25 per visit). Therefore, at the end of research participation, participants are eligible to receive up to US $275. This compensation is intended to facilitate participation without adding undue influence.

### Setting

Treatment-seeking veterans from the Edward Hines Jr VA Hospital will be included. All research procedures will take place at this hospital.

### Participants

We will target the enrollment of 46 veterans with AUD+mTBI. Complete study eligibility criteria are presented in Textbox 1. Veterans aged 22 to 70 years without a history of moderate to severe TBI, neurodegenerative disorders, psychotic spectrum disorders, MRI contraindications, intellectual disability (Wechsler Test of Adult Reading predicted full-scale IQ score <70) [58], or the use of illicit substances in the past 30 days (except for cannabis) will be eligible. The lower age limit was set as 22 years because the FDA considers individuals aged ≥22 years as adults. The upper age limit of 70 years was selected to eliminate potential confounds related to neural aging processes and the potential for neurodegenerative disease onset. Veterans will meet *Diagnostic and Statistical Manual of Mental Disorders, Fifth Edition* (*DSM-5*) [1], criteria for AUD per the Structured Clinical Interview for *DSM-5* [59] and the symptom attribution and classification algorithm (SACA) classification criteria for mTBI. This algorithm, developed by our team [60], is systematic and consistent with the American Congress of Rehabilitation Medicine [12], VA, and Department of Defense mTBI criteria [13].

Participant eligibility criteria.
**Inclusion criteria**
Aged 22 to 70 yearsCan read and speak English*Diagnostic and Statistical Manual of Mental Disorders, Fifth Edition* (*DSM-5*), criteria for alcohol use disorder symptom attribution and classification algorithm (SACA), criteria for mild traumatic brain injury (mTBI; without requirement of clinical neuropsychological impairment)
**Exclusion criteria**
History of moderate to severe TBIWithin 1 year of mTBIHistory of nontraumatic neuroinjury (eg stroke, neurosurgery, or hemorrhage)Neurodegenerative disease (eg, Alzheimer disease, Parkinson disease, or multiple sclerosis)Has an active, unstable health condition (ie, decompensated heart failure or recent severe heart attack)Within 12 weeks of major surgeryHistory of psychosis or current psychosis not attributable to an external cause (eg, illicit drug use)Endorses active suicidal ideation with intent and plan (these participants will be brought to the emergency department for emergent psychiatric care)Intellectual disability (Wechsler Test of Adult Reading predicted full-scale IQ score <70) [58]Is pregnant or nursingUse of benzodiazepines, opiates, cocaine, or amphetamines in the past 30 daysMeets *DSM-5* criteria for moderate to severe cannabis use disorderContraindications to magnetic resonance imaging (eg, claustrophobia, ferromagnetic metal in eyes or face, congestive heart failure, implanted cardiac pacemaker or defibrillator, cochlear implant, or nerve stimulator)Contraindications to intermittent theta burst stimulation and transcranial magnetic stimulation (eg, epilepsy or taking medications that elevate the seizure threshold)Meets SACA criteria for “questionable validity” of performance effort and symptom reporting

To enhance generalizability, veterans will be included irrespective of combat and deployment status. As cannabis use is prevalent among veterans, including those with AUD, cannabis users and those with mild cannabis use disorder (per *DSM-5*) [1,59] will not be excluded; given that legal cannabis purchase and consumption are likely to increase across the United States, the inclusion of cannabis users will increase the generalizability of the findings. As daily cannabis use and cannabis dependence have significant relationships with ARCs, veterans with moderate to severe cannabis use disorder will be excluded. Depression, anxiety, and PTSD commonly co-occur among veterans [61]. As this is the population we seek to generalize our study findings to, participants who meet *DSM-5* [1] criteria for depression, anxiety, or PTSD will not be excluded. To maintain high-quality data, any participant meeting criteria for questionably valid symptom profiles (ie, effort and symptom validity) will be excluded. The forced choice component of the California Verbal Learning Test–Second Edition will be used, with a cutoff score of 15, as a measure of effort performance [62]. The Minnesota Multiphasic Personality Inventory-2–Restructured Form [63] will be used to identify atypical symptom reporting based on the following criteria: infrequency scale T score ≥107, infrequency-psychopathology scale T score ≥85, true response inconsistency scale T score ≥80, and variable response inconsistency scale T score ≥80 [60].

There are no study participation limitations based on gender, race, or ethnicity.

### Recruitment

To recruit a study sample representative of veterans with AUD+mTBI, we will target treatment-seeking veterans from the Edward Hines Jr VA Hospital, which houses a residential SUD treatment program, an outpatient SUD treatment program, and a TBI and polytrauma program (ie, a VA polytrauma network site).

We will identify research candidates at this VA hospital using the national inpatient and outpatient files available through the VA Informatics and Computing Infrastructure. We will request access to data housed in the Corporate Data Warehouse, including production domains and vital status files (such as Beneficiary Identification and Record Locator Subsystem), as well as Compensation and Pension Record Interchange (CAPRI) and Veterans Health Information Systems and Technology Architecture (VistA), with real social security number identifiers located in VA Informatics and Computing Infrastructure using the Data Access Request Tracker system. Once this access is approved, we will search the database for the past 10 years using appropriate *International Classification of Diseases, Ninth Revision* and *International Classification of Diseases, Tenth Revision, Clinical Modification* codes reflecting study inclusion criteria. These files will be accessed for the duration of the study.

After identification, veterans’ medical records will be reviewed for eligibility, and eligible veterans will be mailed an informational letter. The study team will follow up with a telephone call 1 week after the letter is mailed to inquire whether the veteran is interested, and, if so, screen further for eligibility. The study team will also distribute IRB-approved flyers and present the study at relevant staff meetings for VA providers. VA providers will also be given IRB-approved flyers and encouraged to give them to veterans who may be a good fit for the study. The flyers will contain a study contact telephone number so that veterans can call the study team if they are interested in participating.

The veterans with AUD+mTBI who completed the neural TMS site determination phase will be called to schedule research procedures for the rTMS treatment phase. There will be a gap of 1 month to 4 years between the completion of study phases, and quarterly check-in calls will be completed to maintain study contact with participants.

### Data Collection and Measures

#### Overview

Data collection occurred across multiple study time points, beginning with screening and baseline visits and continuing through posttreatment and follow-up visits. The full study timeline is presented in Figure 4. An overview of the assessments collected at each time point is provided in Table 2.

**Figure 4 figure4:**

Study timeline. BL: baseline visit; F1: follow-up time point visit occurring 2 weeks after the last active repetitive transcranial magnetic stimulation (rTMS) session; F2: follow-up time point visit occurring 1 month after the last active rTMS session; F3: follow-up time point visit occurring 3 months after the last active rTMS session; F4: follow-up time point visit occurring 6 months after the last active rTMS session; MT: motor threshold visit; PA: post–active rTMS visit; PS: post–sham rTMS visit; S: screening visit.

**Table 2 table2:** Study assessments, grouped by time point collected.

Time points and assessments administered			Assessment purpose
**Telephone screening**			
	AUDIT-C^a^	Screen for AUD^b^	
	OSU TBI-ID^c^	Screen for TBI^d^	
	TMS^e^ safety form	Screen for TMS safety	
	Medication inventory form	Screen for TMS safety	
**Screening visit**			
	SCID-5^f^ AUD module	Diagnosis and duration of AUD	
	Structured diagnostic interview [60] with the NSI^g^ [64]	mTBI^h^ classification and symptoms	
	CIWA-Ar^i^	Determine acute alcohol withdrawal status	
	TLFB^j^ alcohol calendar, past year	Determine alcohol consumption history	
	C-SSRS^k^	Determine acute suicidality	
**Baseline, post–sham repetitive TMS, post–active repetitive TMS, 2-wk, 1-mo, 3-mo, and 6-mo follow-up visits**			
	WHODAS 2.0^l^	Self-reported functional disability (primary outcome)	
	PACS^m^	Self-reported alcohol craving (secondary outcome)	
	OCDS^n^	Self-reported alcohol craving (secondary outcome)	
	ACQ-NOW^o^	Self-reported alcohol craving (secondary outcome)	
	NSI	Self-reported mTBI symptoms (secondary outcome)	
	PCL-5^p^	Self-reported PTSD^q^ symptoms (secondary outcome)	
	BDI-II^r^	Self-reported depression symptoms (secondary outcome)	
	BAI^s^	Self-reported anxiety symptoms (secondary outcome)	
	MASQ^t^	Self-reported mood and anxiety symptoms (secondary outcome)	
	FTND^u^	Self-reported nicotine use symptoms (secondary outcome)	
	C-SSRS	Determine acute suicidality	

^a^AUDIT-C: Alcohol Use Disorder Identification Test–Consumption Questions.

^b^AUD: alcohol use disorder.

^c^OSU TBI-ID: Ohio State University Traumatic Brain Injury Identification Method.

^d^TBI: traumatic brain injury.

^e^TMS: transcranial magnetic stimulation.

^f^SCID-5: Structured Clinical Interview for *DSM-5*.

^g^NSI: Neurobehavioral Symptom Inventory.

^h^mTBI: mild traumatic brain injury.

^i^CIWA-Ar: Clinical Institute Withdrawal Assessment for Alcohol, Revised.

^j^TLFB: Timeline Follow-Back.

^k^C-SSRS: Columbia–Suicide Severity Rating Scale.

^l^WHODAS 2.0: World Health Organization Disability Assessment Schedule.

^m^PACS: Penn Alcohol Craving Scale.

^n^OCDS: Obsessive-Compulsive Drinking Scale.

^o^ACQ-NOW: Alcohol Craving Questionnaire.

^p^PCL-5: PTSD Checklist for *DSM-5*.

^q^PTSD: posttraumatic stress disorder.

^r^BDI-II: Beck Depression Inventory-II.

^s^BAI: Beck Anxiety Inventory.

^t^MASQ: Mood and Anxiety Symptom Questionnaire.

^u^FTND: Fagerström Test for Nicotine Dependence.

#### Screening

Veterans identified as research candidates will complete an initial telephone screening for the following: (1) probable AUD, using the Alcohol Use Disorder Identification Test–Consumption Questions (AUDIT-C) [65]; (2) probable mTBI, using the Ohio State University Traumatic Brain Injury Identification Method [66]; (3) TMS safety, using our TMS safety form; and (4) self-reported age as well as the ability to read and speak English. Age will be verified in the EMR (ie, Computerized Patient Record System or Compensation and Pension Record Interchange). The AUDIT-C is a 3-item, self-report measure of alcohol use; scores range from 0 to 12, with a score of ≥4 for men and ≥3 for women indicating hazardous drinking and probable AUD. A list of prescribed and over-the counter medications and the length of time the participant has been on each medication will also be collected over the telephone. Current medications will be cross-referenced with study eligibility criteria and the EMR to identify any antiepileptics as well as any medications known to lower seizure threshold. The EMR will also be reviewed for study eligibility criteria. If review findings indicate possible contraindications to rTMS or MRI related to a metal implant, attempts will be made to identify the model and manufacturer of the implant to determine whether it is safe to expose the implant to a strong magnet. Manufacturer recommendations regarding safety will be followed. If potential participants meet all eligibility criteria, they will be scheduled for the first research visit. They will be mailed a copy of the informed consent form to review, along with a reminder of the appointment date and time.

Veterans meeting the initial screening criteria for the AUD+mTBI group will screen positive for the AUDIT-C and report at least 1 lifetime mTBI on the Ohio State University Traumatic Brain Injury Identification Method.

All veterans aged 22 to 70 years without MRI safety contraindications who can read and speak English will be eligible for enrollment and diagnostic screening as outlined in the following paragraphs. Veterans meeting these criteria will complete behavioral assessments during visit 1 that will be used to confirm study eligibility.

We will complete the Timeline Follow-Back alcohol calendar for the past year, meeting with a study physician to review current medications, recent drinking history, the Columbia–Suicide Severity Rating Scale (C-SSRS), and the Clinical Institute Withdrawal Assessment for Alcohol, Revised.

Abstinence from alcohol and illicit substances will be requested for each in-person visit and will be confirmed with a urine alcohol and urine drug screen and breathalyzer or urine or saliva test for alcohol following evolving hospital COVID-19 guidelines. If veterans opt for an in-person visit 1, the urine drug screen will be completed by a VA clinical laboratory using a manual requisition form with the veteran’s unique participant ID number. All subsequent urine drug screens will be conducted by research staff using a urine test kit. The results from the drug and alcohol screens will not be entered into the veteran’s medical record; they are for research purposes only. Urine specimens will not be stored. Participants will also complete an acute cannabis intoxication scale [67] that includes four items: (1) increased resting heart rate (>100 beats per min), (2) congestion of the conjunctival blood vessels (red eyes), (3) slowed speech, and (4) giddiness. Any participant testing positive for alcohol, drugs, or cannabis intoxication will be asked to reschedule research procedures, and safe transportation will be arranged (eg, taxi), or participants will be escorted to the emergency department (ED) or mental health intake, as appropriate.

#### Baseline, Post–Sham rTMS, Post–Active rTMS, 2-Week, 1-Month, 3-Month, and 6-Month Follow-Up Visits

All veterans will complete the primary outcome measure: the WHO Disability Assessment Schedule (WHODAS 2.0), a self-report of functional disability. The following ARCs will also be collected as secondary outcomes: the Penn Alcohol Craving Scale, the Obsessive-Compulsive Drinking Scale, the Timeline Follow-Back (including the number of days between baseline and screening visits), and the Alcohol Craving Questionnaire. The following additional secondary outcomes will also be assessed: the Neurobehavioral Symptom Inventory, the PTSD Checklist for *DSM-5*, the Beck Depression Inventory-II, the Beck Anxiety Inventory, and the Mood and Anxiety Symptom Questionnaire. The C-SSRS will be repeated at baseline, after both sham and active rTMS treatment session 5, and at post–sham rTMS and post–active rTMS visits. We will also assess self-reported smoking status (ie, current, former, or never smoker, with never smoker defined as having smoked <100 cigarettes in a lifetime) and the Fagerström Test for Nicotine Dependence.

Finally, all female participants will complete a urine pregnancy test using a test kit at baseline and post–sham rTMS time points.

We will be using the VA REDCap (Research Electronic Data Capture; Vanderbilt University) secure web application for data collection and data entry. Data will be checked for completeness at the time of assessment and again at the time of data entry. Reasons for missingness will be documented.

### rTMS Intervention

#### Randomization to Stimulation Site Group

Veterans with AUD+mTBI will be randomly assigned to 1 of 2 stimulation site groups: a customized site or left DLPFC. SAS 9.4 (SAS Institute Inc) will be used to develop the randomization protocol for the veterans, ensuring an equal number of participants—assigned sequentially—in each of the 2 groups. An electroencephalography (EEG) cap along with the coordinate Beam F3 method and neuronavigation will be used for each participant to maintain the single-blind design. The randomization scheme will be provided by the biostatistician to a single unblinded administrator (who will not complete any research procedures or analyses). This administrator will inform the rTMS provider of the patient’s assigned site (left DLPFC or a customized site) for rTMS treatment.

The customized site will be one of the sites depicted in Figures 1- 3- as determined by ongoing analyses.

#### MT and Brain Mapping

Each participant’s T1-weighted MRI scan will be loaded into a Localite TMS Navigator system. A MagVenture C-B60 coil will be used to deliver single-pulse TMS to the left motor cortex to identify the abductor pollicis brevis (ie, thumb muscle) coordinates. Resting MT will be guided by adaptive parameter estimation by sequential testing procedures [68] using a web-based tool [69] and defined as the lowest stimulus intensity necessary to produce motor evoked potentials of peak-to-peak amplitude of ≥50 µV in 5 of 10 trials. Motor evoked potentials of the abductor pollicis brevis will be recorded using surface electrodes on the right thumb. MT may be repeated as needed with changes in medication regimens, illness, and so on. The left DLPFC will be mapped using the standard EEG cap and coordinate Beam F3 method [70]. The customized site will be mapped using Montreal Neurological Institute (MNI) atlas coordinates. EEG caps and neural navigation will be used at every rTMS session for blinding purposes. MT procedures will be conducted by a trained TMS administrator.

#### rTMS Parameters

rTMS will be provided at 10 Hz, 4.9 seconds per train, intertrain interval of 30 seconds, 20 total trains per session, and an intensity of 110% MT [41,51,54]. Each patient will receive 1000 pulses per day. The sham and active rTMS sessions will each be provided daily for 2 weeks (once per d, 5 d per wk; Figure 4). If a date is missed, it will be made up as soon as possible at the end of treatment. The rates of missed sessions and durations between sessions will be recorded and used as potential covariates in analyses. rTMS procedures will be conducted by a trained TMS administrator.

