**Conclusions:**

We will be able to provide preliminary evidence of the efficacy, safety, and feasibility of a novel TMS target for veterans with AUD+mTBI.

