### Objectives

This study aims to (1) test the preliminary efficacy of high-frequency rTMS provided to a customized neural target to treat functional disability among veterans with AUD+mTBI and (2) assess the sustainability of rTMS effects on functional disability among veterans with AUD+mTBI.

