#### Covariates

Covariates (eg, age, combat and deployment status, cannabis use, and nicotine dependence) will be used in the model to adjust the effect of the intervention. A bivariate analysis will be performed to test the association between each covariate and the functional disability outcome. Only statistically significant covariates will be included in the regression model.

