#### Statistical Approach

#### Objective 1

A within-participant, longitudinal design will be used in which all veterans will first receive sham rTMS followed by active rTMS applied to the customized neural target and the standard FDA-approved treatment site (left DLPFC). Thus, there will be 2 groups. The primary outcome, functional disability (WHODAS 2.0), will be assessed at baseline, after sham rTMS, and after active rTMS. A mixed effects model, incorporating within-participant correlation from repeated measures, will be used to compare the difference between difference between sham (Figure 4: PS-BL) and active rTMS (Figure 4: PA-PS) treatments. We will compare the aforementioned difference in sham and active rTMS of the left DLPFC neural target or site of stimulation with the customized neural target group.

#### Objective 2

A recovery curve will be constructed based on repeated functional disability (WHODAS 2.0) measures at post–active rTMS, 2-week, 1-month, 3-month, and 6-month follow-up time points (Figure 4: PA, F1–F4). A mixed effects model (incorporating within-participant correlation from repeated measures) will be used to examine change (using the slope of the model) in WHODAS 2.0 from post–active rTMS to each follow-up time point for each group. We will examine the change in slope of the left DLPFC group compared to the customized neural target group using WHODAS 2.0 measures from post–active rTMS to each follow-up time point.

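### Missed sessions and treatment gaps, which arise after randomisation, are named as possible covariates and nothing keeps them out of the randomised site comparison

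*Protocol article*

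**What the plan says.** Randomisation to Stimulation Site Group allocates veterans to one of two sites, "ensuring an equal number of participants—assigned sequentially—in each of the 2 groups". Every participant has a sham block and then an active block.

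Under Statistical Approach, Objective 1 takes the WHODAS 2.0 change over the sham block and over the active block, and then sets the groups against each other: "We will compare the aforementioned difference in sham and active rTMS of the left DLPFC neural target or site of stimulation with the customized neural" (the last words of the sentence are cut here). The slopes of the two groups after treatment are compared under Objective 2.

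On attendance, rTMS Parameters has two consecutive sentences. First: "If a date is missed, it will be made up as soon as possible at the end of treatment". Then: "The rates of missed sessions and durations between sessions will be recorded and used as potential covariates in analyses".

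The Covariates section says that covariates "will be used in the model to adjust the effect of the intervention". It describes a bivariate test of each covariate against functional disability and ends: "Only statistically significant covariates will be included in the regression model". Its examples are age, combat and deployment status, cannabis use and nicotine dependence. The list is open, and nothing is said about when a covariate must have been measured.

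The Abstract's conclusions promise "preliminary evidence of the efficacy, safety, and feasibility of a novel TMS target". The Objectives section names efficacy and sustainability only.

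**The concern.** Site is the randomised factor, so an analysis that leaves out post-randomisation variables estimates the total effect of being assigned to one site rather than the other. Missed sessions and gaps come after assignment, and the protocol itself contains two routes by which site could influence them:

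- **Discomfort.** Safety Measures asks for a pain rating after every session. If one site is less comfortable, it may produce more missed or delayed sessions.
- **Drinking.** The Screening section asks for abstinence at each in-person visit and reschedules anyone who tests positive. Alcohol use is a secondary outcome. If one site reduces drinking more, it may also produce fewer gaps.

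On either route, adjusting for attendance takes out part of what the site did. Any unmeasured factor that drives both attendance and disability adds a further distortion. The admission rule in the Covariates section makes this more likely, because it favours variables that track the outcome. The pilot's data are meant to inform power calculations for larger studies, so a distorted site effect would be carried forward.

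**Working it through.** **Inputs from the protocol.** Target enrolment is 46, taken as 23 per arm because the groups are to be equal. The effect size of 0.65 comes from Sample Size Justification. It was set for the target identification phase and serves here only as an example of a true effect.

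The 46 can be reproduced. Two-sided 5% and 80% power give 2 × (1.960 + 0.842)² / 0.65² ≈ 37.2, so 38 per group, and 38 × 1.2 = 45.6, so 46. This reads 46 as one group of a two-group comparison, which is an assumption. The present point does not depend on it.

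**Assumptions (no adherence data are given).** Z is site (0 or 1). M is missed sessions in SD units. Y is improvement in SD units. U is an unmeasured common cause. T is the total site effect.

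- M = aZ + uU + error, with within-arm variance 1
- Y = cZ + bM − uU + error, with within-arm variance 1 and T = c + ab
- a = 0, 0.3, 0.5 or 0.8; b = −0.3 or −0.5; u = 0 or 0.4

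**Formula.** Within an arm, the expected U given M is u(M − aZ). Regressing Y on Z and M therefore gives a site coefficient of c + au² = T + a(u² − b). The unadjusted coefficient is T. The distortion is a(u² − b), which is zero when a = 0.

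For a = 0.3:

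- smallest: 0.3 × (0 + 0.3) = 0.09, so 0.65 becomes 0.74 and 0 becomes 0.09
- largest: 0.3 × (0.16 + 0.5) = 0.198, so 0.65 becomes 0.85 and 0 becomes 0.20

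**Simulation.** 46 participants, 1500 runs per scenario, a simple two-group comparison. Ranges are over the four combinations of b and u. "If significant" applies the Covariates rule (bivariate association with the outcome at two-sided 5%).

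| Site shift in missed sessions (a) | Truth 0.65: always adjusted | Truth 0.65: if significant | Truth 0: always adjusted | Truth 0: if significant |
|---|---|---|---|---|
| 0 | 0.65–0.66 | 0.64–0.65 | 0.00–0.01 | 0.00–0.01 |
| 0.3 SD | 0.74–0.85 | 0.69–0.85 | 0.08–0.20 | 0.06–0.20 |
| 0.5 SD | 0.80–0.98 | 0.70–0.97 | 0.15–0.33 | 0.11–0.33 |
| 0.8 SD | 0.88–1.17 | 0.70–1.13 | 0.26–0.53 | 0.17–0.53 |

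The unadjusted estimate stayed at 0.64–0.66 when the truth was 0.65, and within 0.03 of zero when the truth was 0. The significance rule admitted missed sessions in 17% to nearly 100% of runs, depending on the scenario.

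**Direction.** The table has the site coded 1 causing more missed sessions, so adjustment flatters that site. If that site causes fewer (a = −0.3), the formula gives −0.09 to −0.198, and 0.65 falls to 0.56–0.45. The sign cannot be known in advance.

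**Sample size.** The formula does not contain n. Fewer participants would change how often the covariate is admitted, but not the distortion once it is in the model.

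**The case against.** The strongest reply is that the plan commits to nothing. The covariates are only potential, no model is named, the listed examples do not include attendance, and a statistical analysis plan not shown here may settle the matter. That much stands: a reader might infer that attendance will certainly be adjusted for, and the text does not say so. What remains is that the only admission rule in the document is association with the outcome, with no condition on timing. Following the protocol as written can therefore put these variables into the site comparison.

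Second, a reader might infer that attendance is a result of the assigned site. The documents do not show this. Rescheduling after a positive test need not differ by site. Misses in the sham block are less likely to, since the sham sensation comes from forehead electrodes. With no site effect on attendance the check finds no bias.

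Third, it is tempting to say that two missed sessions out of ten would remove 20% of the effect. The make-up rule defeats that: a missed date is meant to lengthen the course, not shorten it. Nor would a loss of benefit through missed sessions be the same quantity as the bias from adjusting for them.

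Fourth, a reader might infer that attendance is the only evidence behind the feasibility statement, and that the plan is at fault for giving no feasibility endpoint or progression threshold. Pain ratings, the per-session safety log, the adverse event log and the promised CONSORT diagram also bear on it. Recording attendance does not prevent reporting it by arm, and an article commonly leaves feasibility definitions and thresholds to the full protocol or analysis plan.

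**Conclusion.** The point holds in a conditional form. The protocol names two post-randomisation adherence measures as possible covariates, and its selection rule does not exclude them from the randomised comparison. If the assigned site affects attendance, the adjusted estimate is no longer the total effect of site on WHODAS 2.0. If it does not, no bias is expected.

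The size depends on assumed values. With a 0.3 SD site shift in missed sessions, a true 0.65 SD becomes 0.74–0.85 and a true null becomes 0.08–0.20 when the covariate is in the model. Applying the significance rule lowers the bottom of those ranges to 0.69 and 0.06. Larger shifts give larger distortions, and the direction reverses if the site reduces missed sessions. These figures come from a linear two-group model, not from the planned mixed model, and illustrate the mechanism only. The correction is worth making because it removes the risk at almost no cost.

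**What to change.** In rTMS Parameters and Covariates, state that the models comparing sites on WHODAS 2.0 and on the secondary outcomes will use only covariates measured before randomisation. For measures repeated during the trial, such as the nicotine dependence score, use the baseline value.

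Replace the covariate role of missed sessions and between-session durations with descriptive reporting by arm and by block (sham, active). This also informs the feasibility statement in the Abstract. Label any analysis that adjusts for adherence as exploratory or as a sensitivity analysis.

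The data are already to be recorded and the target of 46 is unchanged, so the cost is wording. The downside is that any precision gained from adherence covariates is given up in the main analysis.
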